### Randomization and blinding

There are two investigators at each center (referred to as A and B). Investigator A is responsible for entering baseline data of patients and perform randomization, but he will not know the grouping details and will not participate in the treatment. Investigator B is responsible for performing treatment according to the grouping. At each visit, A is responsible for collecting data and entering the data in the electronic data capture (EDC) system. The therapist and the data collector are separate. Statisticians are responsible for data processing and are not aware of the grouping until the end of the trial. Central randomization will be conducted by CLINDA Soft Co., Ltd. (Tianjin, China). A random sequence will be generated with SAS 9.2 (SAS Institute, Inc., Cary, NC, USA) by an independent statistician who is not involved in the study; the sequence will be stored in a central randomization system (interactive web response [IWR] system). Patients will be stratified based on the three different centers and randomly assigned to the crossbow needle group and the acupuncture group in a 1:1 ratio. The crossbow needle group will receive crossbow needle therapy. Regular acupuncture therapy will be performed on the acupuncture group.

In this trial, patients will not be blinded due to the uniqueness of the two therapies. Investigators and statisticians will be blinded. Treatment, data collection, and data analysis will be conducted by trained practitioners, data collectors, and statisticians, respectively, all blinded to one another in order to ensure the reliability of the results.

The conditions for unblinding are: (1) infection or other adverse events (AE)—and these patients will be withdrawn from the trial; or (2) the end of the trial and data analysis.

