### Interventions

Patients in both groups will receive two sessions (ten times a session) of treatment. The treatment will be performed every other day, three times per week, 20 times in total. The first follow-up will be conducted 15 days after the last treatment, followed by a second follow-up 15 days later. All practitioners involved in the trial are trained and registered professionals. A training program to standardize all manipulations and filling of a case report form (CRF) will be provided before the trial. Investigators will inform all patients about the possible inconveniences from the trial.

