### Crossbow needle group

Before treatment, a prescription of herbs containing Sheng Cao Wu (*Radix Aconiti Kusnezoffii*) (20 g), Tou Gu Xiang (*Gaultheria yunnanensis*) (50 g), Hei Gu Teng (*Periploca forrestii*) (30 g), and Ba Jiao Feng (*Alangium chinense*) (15 g) will be ground into a powder, put into a glass container, and soaked in 1000 mL of 50%-proof white liquor for seven days. The obtained clear brown liquid is effective in dispelling wind and eliminating dampness, dispersing numbness and relieving pain, dredging collaterals, and promoting blood circulation [15–18]. Patients in this group will receive crossbow needle therapy. The treatment will use 0.22 × 1.0-mm skin needles (Cloud & Dragon Medical Device Co., Ltd., Wujiang, Zhejiang, China). A practitioner will soak the skin needles in the brown herbal liquid for 10 min before treatment. Patients will be asked to take a supine or sitting position. The soaked skin needles will be applied on the square knee area formed by Xuehai (SP10), Liangqiu (ST34), Yanglingquan (GB34), and Yinlingquan (SP9), with the patella as the center, moving in different directions (Fig. 3). One completion of rolling the skin needle in all directions as displayed in Fig. 3 is seen as one set of application. Skin needles will be dipped into 5 mL of herbal liquid every five sets of application until the liquid is used up. The intensity of application varies from person to person, depending on the tolerance of the patients.

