### Statistical analysis

Data analysis will be conducted in accordance with the intention-to-treat principle. Missing data will be handled using linear mixed effects models. Statisticians and chief investigators will work out an analysis plan and related forms before database lock. The analysis will include case distribution, comparison of basic values, compliance, effectiveness, factors that influence efficacy, and safety. Statistical analysis will be conducted using SAS 9.2 (SAS Institute Inc., Cary, NC, USA). The Wilcoxon rank sum test, *t* test, or variance analysis will be performed for inter-group or intra-group comparison according to data distribution. The Wilcoxon rank sum test will be used to compare ranked data. The chi-square test will be applied to compare enumeration data. All tests will be one-sided. A *p* value < 0.05 will be considered statistically significant.

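### Randomisation is stratified by centre, but centre is in none of the named between-arm tests or models; if centres differ, the test is conservative and loses a little power.

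*Protocol article*

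**What the plan says.** The Randomization and blinding section makes centre the stratification factor: "Patients will be stratified based on the three different centers and randomly assigned to the crossbow needle group and the acupuncture group in a 1:1". There are three centres, and no other factor is named.

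The Statistical analysis section names the tests. For continuous outcomes: "The Wilcoxon rank sum test, *t* test, or variance analysis will be performed for inter-group or intra-group comparison according to data distribution". For counts: "The chi-square test will be applied to compare enumeration data". No stratified form of any test is given. Linear mixed effects models are named for handling missing data, without their terms. The same section also plans to look at what affects efficacy, without listing the factors, and promises an analysis plan before database lock.

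Centre is not named as an analysis factor anywhere in the article.

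**The concern.** Allocation forced to balance within centre removes between-centre differences from the sampling variation of the arm difference. A two-sample t test does not know this. Its standard error uses the total spread, including the part due to centre, so it overstates the uncertainty of the estimate. The unstratified rank-sum and chi-square tests set the stratum aside in the same way.

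What is at stake is efficiency and the accuracy of the stated error rate. The design does the work of balancing centres, and the named tests do not use it. In a non-inferiority trial, an interval that is too wide can miss the margin when a correctly calculated one would clear it.

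**Working it through.** **Inputs from the Sample size section:** one-sided alpha 0.05 (1.645), beta 0.10 (1.282), margin 1.5, SD 4.0, 20% dropout.

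**The plan's own figure:** n = 2 × [(1.645 + 1.282) × 4.0 / 1.5]² = 121.85, so 122 per arm. Then 122 / 0.80 = 152.5, so 153 per arm and 306 in total. Both stated figures reproduce, and neither depends on centre.

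**Assumed input:** the share r of outcome variance that lies between centres. The article does not give it, so r is taken as 1%, 5%, 10% and 20%.

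**Formulas,** by normal approximation, with 4.0 as the total SD and balance within centre:
- Unadjusted SE = 4.0 × √(2/122) = 0.512, and k = 1.5 / 0.512 = 2.929.
- The true SE uses the within-centre SD, 4.0 × √(1 − r), so the unadjusted SE is too large by the factor 1/√(1 − r).
- Actual one-sided error = Φ(−1.645 / √(1 − r)).
- Unadjusted power = Φ((k − 1.645) / √(1 − r)).
- Power with centre in the model = Φ(k / √(1 − r) − 1.645).

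For example, at r = 0.10, √0.90 = 0.9487. The error is Φ(−1.734) = 4.1%, unadjusted power is Φ(1.353) = 91.2%, and adjusted power is Φ(3.087 − 1.645) = 92.5%.

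| Centre share r | SE too wide by | Actual one-sided error | Power, unadjusted | Power, adjusted | Power lost (points) |
|---|---|---|---|---|---|
| 1% | 0.5% | 4.9% | 90.2% | 90.3% | 0.1 |
| 5% | 2.6% | 4.6% | 90.6% | 91.3% | 0.7 |
| 10% | 5.4% | 4.1% | 91.2% | 92.5% | 1.3 |
| 20% | 11.8% | 3.3% | 92.4% | 94.8% | 2.4 |

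**Sensitivity to the meaning of 4.0.** The article calls it a combined SD and does not split it. If it is the within-centre SD, adjusted power is 90.0% throughout and unadjusted power is 89.9%, 89.3%, 88.4% and 86.2%. The loss is then 0.1 to 3.8 points, with the same error rates as above.

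**Simulation check,** on the within-centre reading: 20,000 trials, three centres, 41 patients per arm per centre. At r = 20% the unadjusted test had error 3.9% and power 87.6%. With centre in the model these were 5.0% and 90.1%. The direction agrees. The effect is milder than the formula gives because, with only three centres drawn at random, their realised variance averages two thirds of the assumed value.

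**The case against.** **The detail may belong to the later plan.** Model terms are often left to an analysis plan, and one is promised. Variance analysis and the mixed model could both carry centre, and the planned look at influences on efficacy could include it. This stands in part: the article does not say that centre will be left out. But it goes beyond silence. It names specific tests, chosen by data distribution, and where the t, rank-sum or chi-square test is chosen as written, the stratum has no place.

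**The harm is small and in the safe direction.** This stands. With 4.0 as the total SD, unadjusted power stays above the planned 90% in every scenario, and the size rests on assumed centre shares.

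**A reader might infer that each centre has a single operator whose skill distorts the comparison.** The text does say "There are two investigators at each center (referred to as A and B"), and that "Investigator B is responsible for performing treatment according to the grouping". But B is a role, and the Interventions section uses the plural: "All practitioners involved in the trial are trained and registered professionals". B's role covers treatment in both arms, so a general operator effect is shared and cancels under 1:1 allocation within centre. The statement that "The intensity of application varies from person to person, depending on the tolerance of the patients" describes differences between patients and is not evidence of operator dependence. Delivery is also to be standardised: "A training program to standardize all manipulations and filling of a case report form (CRF) will be provided before the trial". The acupuncture follows a national standard of manipulation.

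**A reader might also infer that a poor result at one centre would stay hidden.** That concerns a treatment effect that differs by centre, which is a separate question. An additive centre term would not remove it, three centres estimate it poorly, and nothing in the article rules out results by centre.

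**Conclusion.** The point holds as a mismatch between the randomisation and the named tests, with modest consequences. For assumed centre shares of 1% to 20%, with 4.0 as the total SD, the standard error is 0.5% to 11.8% too wide, the one-sided error is 4.9% to 3.3% against a nominal 5%, and 0.1 to 2.4 points of power are lost. If centres do not differ in outcome, nothing is lost.

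It would be wrong to read this as a bias or as a route to false non-inferiority. Differences in level between centres cancel in the arm comparison, and the error they cause is conservative. The sample size is unaffected.

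**What to change.** In the Statistical analysis section, or in the promised analysis plan before database lock, state that the primary WOMAC non-inferiority comparison includes centre, the randomisation stratum, as a fixed effect in the linear mixed model or variance analysis. Where a rank test is used, make it the stratified (van Elteren) form. Where a chi-square test is used, make it Cochran-Mantel-Haenszel. The model is the simpler route, because it gives directly the interval to set against the margin of 1.5. Differences by centre, with intervals, may be reported descriptively.

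The cost is one sentence and two degrees of freedom. Centre is already known from the randomisation, so no new data or patients are needed. The choice should be fixed before unblinding, so that adjustment cannot be decided after the results are seen.

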### Adherence

Before the start of the trial, the investigators will fully inform the patients of the benefits and the possible inconvenience of the study. The patients will sign the informed consent form and volunteer to participate in the study. Anteroposterior and lateral X-ray of the knee, laboratory examination, and two courses of treatment will be free of charge in order to improve the adherence of the patients. The baseline data of each patient (name, gender, age, address, telephone or contacts of immediate family members) will be recorded in detail, hereby to facilitate the supervision of patients’ adherence. The cases of drop-out, withdrawal, and discontinuation will be recorded and followed up by telephone or even followed up at patients’ homes if necessary.

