### Safety monitoring

Possible AEs during crossbow needle treatment include itching, redness, and swelling. Fainting, sticking of needle, hematoma, subcutaneous hematoma, and bleeding might occur during acupuncture treatment. Any AE that occurs during the trial will be recorded in a CRF by researchers and patients will be treated as soon as possible. Patients may choose to withdraw from the trial due to any AE. The sponsor and the data management company CLINDA will monitor the implementation of the trial protocol and filling of CRFs.

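### Any adverse event, however mild, is made a ground for unblinding and compulsory withdrawal, in conflict with the safety section and at odds with intention-to-treat

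*Protocol article*

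**What the plan says.** The rule stands in the protocol article under Randomization and blinding: "The conditions for unblinding are: (1) infection or other adverse events (AE)—and these patients will be withdrawn from the trial". The other condition for unblinding is the end of the trial and data analysis. The adverse event condition carries no qualifier of severity, seriousness or relation to treatment, and the text does not say who receives the code.

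The same section describes who knows the allocation. On patients: "In this trial, patients will not be blinded due to the uniqueness of the two therapies". On the therapist: "Investigator B is responsible for performing treatment according to the grouping". Investigator A collects the data and is not to know the grouping. On the analysts: "Statisticians are responsible for data processing and are not aware of the grouping until the end of the trial".

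Safety monitoring handles the same events differently. They are recorded on the case report form and treated, and then: "Patients may choose to withdraw from the trial due to any AE". It also names the events to be expected. For the experimental arm: "Possible AEs during crossbow needle treatment include itching, redness, and swelling". For acupuncture it lists fainting, a stuck needle, hematoma and bleeding.

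Statistical analysis states: "Data analysis will be conducted in accordance with the intention-to-treat principle". Missing data are to be handled with linear mixed effects models. Adherence adds: "The cases of drop-out, withdrawal, and discontinuation will be recorded and followed up by telephone", with home follow-up if necessary. It does not say that WOMAC is collected at those contacts.

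**The concern.** There are two separate problems.

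**Withdrawal.** One section makes leaving the trial compulsory after an adverse event and another makes it the patient's choice. A site that sees local redness cannot follow both, and the three centers may resolve the conflict differently. Under the compulsory version, patients leave because of something the randomized treatment did to them. Their later WOMAC scores are then missing for a reason tied to treatment and possibly to outcome. The expected events differ in kind between arms, so the loss could be unequal. In a non-inferiority trial with a narrow margin, selective loss of patients who tolerate treatment badly can move the comparison in either direction.

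**Unblinding.** A code is normally broken so that someone can manage the patient. Here the patient and the therapist already know the arm. The only people described as masked who could newly learn it are the data collector and the statisticians, and neither needs it for care.

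For any one patient the two harms are alternatives. If the patient leaves and is not assessed, the outcome is lost. If the data collector still assesses, that person may know the arm. WOMAC is a questionnaire answered by unblinded patients, so masking the data collector protects only in part, and loss of outcomes is the larger worry.

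**Working it through.** **The sections side by side**

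| Question | Randomization and blinding | Other section |
|---|---|---|
| Which events? | Infection, or any other adverse event | Safety monitoring: any adverse event, with mild local reactions named as expected |
| What follows? | Unblinding and compulsory removal | Safety monitoring: record, treat, patient may leave |
| Who lacks the allocation? | Investigator A and the statisticians | – |
| When do statisticians learn it? | Only at the end of the trial | – |
| Outcomes after withdrawal? | Not addressed | Adherence: follow-up contact, WOMAC not mentioned |

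The general statement that investigators are blinded cannot apply literally to Investigator B, who delivers the treatment. An adverse event code break given to the statisticians would contradict the same section's statement about them.

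**The plan's own numbers** (Sample size section: one-sided alpha 0.05, beta 0.10, margin 1.5, SD 4.0, dropout 20%)

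- Evaluable per arm: 2 × [(1.645 + 1.282) × 4.0 / 1.5]² = 121.85, rounded up to 122. This reproduces the plan.
- Enrolled per arm: 122 / (1 − 0.20) = 152.5, rounded up to 153, or 306 in total. This also reproduces.
- Dropout allowance: 153 − 122 = 31 per arm for all causes. It is not broken down, so it may already include adverse event withdrawals.

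**How far a literal rule could reach.** The documents give no adverse event rate. Each patient has 20 treatments (Interventions section). If sessions are assumed independent with event probability q, the share of patients with at least one event is 1 − (1 − q)^20. For q = 0.5%, 1% and 2% this gives about 10%, 18% and 33%. These are assumed rates, shown only because small per-session risks accumulate.

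**Illustrative shift in the comparison.** Suppose withdrawn patients would have scored D points worse than those remaining, by the same amount in both arms. A comparison of the remaining patients then moves by

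shift = (difference in withdrawal proportion) × D,

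in favor of the arm that loses more patients. D is taken as 2 or 4 points, that is 0.5 or 1 times the planning SD of 4.0.

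| Difference in withdrawal | D = 2 | D = 4 | Share of the 1.5 margin |
|---|---|---|---|
| 0 points | 0 | 0 | 0% |
| 5 points | 0.05 × 2 = 0.1 | 0.05 × 4 = 0.2 | 7% to 13% |
| 10 points | 0.10 × 2 = 0.2 | 0.10 × 4 = 0.4 | 13% to 27% |

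The zero row is not a lower bound: if D differed between arms, a shift could arise even with equal withdrawal. If withdrawn patients were no worse than the rest in either arm, there would be no shift at all.

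**Power.** If the 20% already covers these withdrawals, power is unchanged. If 5% or 10% of those otherwise retained were lost in addition, 153 × 0.80 × 0.95 = 116 or 153 × 0.80 × 0.90 = 110 per arm would remain, and power would fall from 90% to about 89% or 87%. No power loss is claimed here, since the extra loss is an assumption.

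**The case against.** The strongest reply is that the two sections can be reconciled. Safety monitoring governs every adverse event, while the unblinding clause concerns only events grave enough for the code to be broken. On that reading nobody is removed for itching, and thresholds are a detail that a condensed article leaves to the full protocol. The text does not support this. It makes the event itself the condition for breaking the code, and it extends the condition beyond infection to other events without limit. This is a rule the article states, not one it leaves out. If a threshold was intended, the clause still needs one.

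Several narrower objections do stand:

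- Withdrawal is in tension with intention-to-treat but does not formally contradict it. The mixed model reduces the problem to the extent that earlier scores predict the missing ones.
- The recipient of the code is not stated, so exposure of the data collector or statisticians is inferred from who remains masked. Nor does the article say that Investigator B manages events; the section on combined use of drugs speaks of clinicians.
- Nothing in the documents shows that patients with local reactions would score 0.5 to 1 SD worse. The plan itself says that its margin and SD rest on expert consensus and are not yet clear. The table is an illustration and no estimate.
- Patients who take other treatment for aggravated symptoms are also withdrawn (Combined use of drugs). That route is tied more directly to poor outcome, and correcting the adverse event clause does not close it. Equally, its existence does not remove the present defect.

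**Conclusion.** The concern holds. The article sets a rule that, applied as written, unblinds and removes randomized patients for any adverse event, including mild reactions it expects treatment to cause. The rule conflicts with the safety section, works against the promised intention-to-treat analysis, and prescribes an unblinding with no evident use in care.

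The size and direction of the effect on the result cannot be determined. The shift of up to 27% of the margin rests wholly on assumed withdrawal differences of up to 10 percentage points, an assumed deficit of 2 to 4 points that is equal in both arms, and an analysis of remaining patients only. Unequal loss between arms is possible but not shown. The conflict between the sections depends on none of these figures. The point should be corrected, because the remedy is cheap and the loss of outcomes it prevents cannot be repaired at analysis.

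**What to change.** Amend the protocol as follows:

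1. Remove adverse events as a reason to unblind the data collector or the statisticians. Those treating the patient already have the allocation and manage the event with it.
2. Replace compulsory withdrawal with discontinuation of study treatment where clinically needed. Bring Randomization and blinding into line with Safety monitoring, so that leaving the trial is the patient's decision.
3. State that Investigator A continues to collect WOMAC at the end of treatment and at both follow-ups from consenting patients who have stopped treatment, by telephone or at home if needed, and that these scores enter the intention-to-treat analysis.

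The cost is a short amendment and modest extra collection work. Adherence already foresees telephone and home contact with withdrawn patients, so the route exists, but completing WOMAC that way may change the mode of administration. The gain in masking is partial, because some events, such as a stuck needle, reveal the arm anyway. The Trial status section reports recruitment since April 2016 and still open, so the amendment protects data still to be collected and cannot recover outcomes already lost.

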### Interventions

Patients in both groups will receive two sessions (ten times a session) of treatment. The treatment will be performed every other day, three times per week, 20 times in total. The first follow-up will be conducted 15 days after the last treatment, followed by a second follow-up 15 days later. All practitioners involved in the trial are trained and registered professionals. A training program to standardize all manipulations and filling of a case report form (CRF) will be provided before the trial. Investigators will inform all patients about the possible inconveniences from the trial.

